### Elimination and Withdrawal Criteria

Misdiagnosis;Those who fail to follow the prescribed treatment or for whom there is incomplete data that would affect the efficacy evaluation and safety evaluation;Subjects with poor compliance, or who use self-administered antidepressants and sleeping pills during the course of treatment, or change the treatment method on their own.

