### Participants

Participants will be recruited by advertisement and doctor referrals from psychology department clinics. Interested individuals can contact research assistants by email or phone. A series of criteria and prerequisites will be sent to the prospective volunteers for filtering the most eligible subjects. First, registration information and pre-selection query forms with Self-rating Depression Scale (SDS), Pittsburgh Sleep Quality Index (PSQI), and Self-rating Anxiety Scale (SAS) will be sent to registered volunteers. Volunteers will be required to complete the form as a first-round selection prior to scheduling a first visit. This visit will further screen and evaluate a volunteer's eligibility according to inclusion criteria (**Table 1**). Research assistants will collect signed consent forms from volunteers who meet all prerequisites and agree to participate in the trial. Patients will not be included in the study if they meet one of the exclusion criteria (**Table 2**).

**Table 1 T1:** Inclusion criteria.

No	Item	Answer
1	18<age<55	□Yes
		□No
2	Presence of ≥ 1 but < 5 symptoms required for the diagnosis of major depression as detailed in the Diagnostic Statistical Manual of mental disorders (DSM-V), including loss of enjoyment/interest, marked tiredness or reduction of energy, agitation or psychomotor retardation, feelings of worthlessness or guilt, sleep disorders, reduced concentration, loss of appetite and body weight, loss of libido, recurrent suicidal thoughts;	□Yes
		□No
3	symptoms lasting at least 2 weeks	□Yes
		□No
4	BDI-II score≥14 points (24)	□Yes
		□No
5	HAMD-17 score: 7 points ≤ HAMD total score < 17 points (25)	□Yes
		□No

**Table 2 T2:** Exclusion criteria.

No	Item	Answer
1	Patients diagnosed with depression, previous mental illness, or organic mental disorders	□Yes
		□No
2	Patients suffering from serious diseases such as heart, brain, liver, kidney, or hematopoietic system disease	□Yes
		□No
3	Women during pregnancy and lactation or women of childbearing age who have fertility intentions	□Yes
		□No
4	Patients with depressive episodes caused by psychoactive substances and non-addictive substances	□Yes
		□No
5	Patients prescribed other drugs or therapies for treating depression during the trial	□Yes
		□No
6	Individuals addicted to alcohol or other drugs	□Yes
		□No
7	Patients with strong suicidal ideation	□Yes
		□No
8	Patients who are participating in other clinical trials at the same time	□Yes
		□No

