### Observation Criteria That Would Stop the Trial

Fail to adhere to the treatment requirement;Cases with serious adverse events that are not suitable for continued treatment;Serious clinical complications that occur in other clinical trials;The progression of disease during treatment.

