### EA Group

Participants will receive 24 sessions of acupuncture treatment (three times a week for 6 weeks; 30 min a session; **Figure 2A**). According to traditional Chinese medicine theory, animal experiments (28, 29), and based on mutual consensus from clinical expert meetings, we will use acupoints GV20, GV29, and bilateral acupoints GB13 (**Figure 2B**) in the treatment. Disposable stainless steel needle insertion will be followed by performed stimulation, such as lifting and thrusting the needle combined with twirling and rotating the needle sheath (as shown in **Figures 2C**, **D**, the operation parameters of depth and frequency will be analyzed by acupuncture manipulation parameter tester [ATP-II; Shanghai Shangyou Medical Equipment Co. Ltd, Shanghai, China]), to produce the sensation known as deqi (sensation of numbness, soreness, radiating, or distention, which is considered to indicate effective needling) (30). One EA wire will be connected to the needle on acupoints GV20 and GV29, and another wire will be connected to the bilateral acupoints GB13. A continuous wave will be provided with a stimulation frequency of 2 Hz (31–33) and an intensity varied from 3 to 5 mA (34) until patients feel comfortable. Acupuncture will be performed by licensed acupuncturists with more than 3 years of clinical experience.

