### Combination Therapy Group

Participants will receive 24 sessions of EA treatment (three times a week for 6 weeks; 30 min a session) combined with individual counseling (once a week for 6 weeks; 50–60 min a session). Treatment details are the same as the EA and the counseling mentioned above.

Patients will be discouraged from any extra treatment beyond this trial requirement. If this trial does not show an obvious effect after 2 weeks of treatment (HAMD 17 scale score maintained at 7–17 points), or a patient's symptoms have worsened (HAMD 17 scale score > 17 points), we will then consider drug intervention to ensure the safety of the patients. At this point, participants will be forced to stop the trial, and relevant data will be analyzed for intention-to-treat (ITT). Prescription drugs will be assessed under the guidance of a psychiatrist. Such assessment will need to fully consider the physiological characteristics of patients, including age, physical condition, drug tolerance, presence or absence of comorbidities, and prescribing based on guidelines for depression or relevant clinical consensus.

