### Statistical Analysis

Statistical analysis will be performed by qualified statisticians in a blinded manner using Statistical Product and Service Solutions (SPSS) software (IBM Corporation, Version 21.0). An ITT analysis will be performed. The baseline comparability of the three groups will be assessed on demographic and clinical characteristics, as well as baseline data. Analysis of variance will be used to compare the mean changes between groups from baseline to each time point. The withdrawal of any subjects from clinical trials will be statistically described one by one. The missing data of a withdrawn patient will be randomly filled with the filling method based on the principle of multiple imputations (34). Continuous variables will be represented by mean ± standard deviation. The data before and after treatment in the group will be compared based on a paired *t*-test, and the comparison between groups will be performed using an independent sample *t*-test. When data are not normally distributed, a Wilcoxon rank sum test or Fisher's exact test will be performed. Multiple measurements of the same indicator at different times will use repeated measures data analysis of variance. Categorical variables will be expressed as frequency (%). Two-tailed *p* values < 0.05 will be considered as statistically significant. Safety will be assessed by adverse events and tabulations of adverse drug reactions and descriptive statistics will be performed. Age and intervention assessment are continuous variables, and their correlation will be analyzed using Pearson correlation coefficients. Treatment duration and gender are graded variables, and the spearman correlation coefficient will be used for the correlation analysis of the intervention assessment. To further evaluate the credibility of the blind method. We will evaluate the implementation of the blind method by trial participants' guesses about the allocation of treatment plans, that is, forcing evaluators and statistical analysts to guess the groups to which the subjects are assigned, and then calculate the Blinding Index Scale based on the guess results (39). In order to balance the heterogeneity of patients from different research centers, we will first analyze the differences between the clinical effects of different interventions in each subcenter. If the conclusions of the subcenters are consistent, there will be no central effect. If the conclusions of the sub-centers are inconsistent, a logistic regression analysis will be performed, and the center will be adjusted as a covariate to analyze the results of interventions and clinical assessment (40, 41).

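### The elimination criteria, most naturally read as removing randomised patients from evaluation, conflict with the stated ITT analysis and multiple imputation and need to be reconciled

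*Protocol article*

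**What the plan says.** Five places in the Methods of the protocol article bear on who is analysed.

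- **Elimination and Withdrawal Criteria.** Besides misdiagnosis, the list has "Those who fail to follow the prescribed treatment or for whom there is incomplete data that would affect the efficacy evaluation and safety evaluation". A further item in the same list reads "Subjects with poor compliance, or who use self-administered antidepressants and sleeping pills during the course of treatment, or change the treatment method on their own". All of these are events that arise once a patient is enrolled.
- A separate list, under **Observation Criteria That Would Stop the Trial**, has as its first item "Fail to adhere to the treatment requirement".
- **Combination Therapy Group, second paragraph.** When drug intervention is considered for lack of effect or worsening, "participants will be forced to stop the trial, and relevant data will be analyzed for intention-to-treat (ITT").
- **Statistical Analysis.** The section states "An ITT analysis will be performed". For withdrawals it adds "The missing data of a withdrawn patient will be randomly filled with the filling method based on the principle of multiple imputations", and each withdrawal is also to be described individually.
- **Participants, Table 2, item 5.** An exclusion criterion reads "Patients prescribed other drugs or therapies for treating depression during the trial".

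No section says how a patient eliminated under the first list is analysed.

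**The concern.** If elimination means leaving the evaluation, the patients whose missing data would be imputed are largely those who have been removed, and an analysis without the non-adherent is not ITT. The primary set would then depend on events after randomisation: adherence, self-treatment and completeness of data.

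Two features of the design make this matter. Allocation is open to physicians and data collectors (Blinding section), so a judgement that compliance is poor may be made with the arm known. The schedules also differ in burden: 6 counselling sessions in one arm, three EA sessions a week for 6 weeks in another, and both in the third. The Trial Objective section infers whether EA has an effect of its own from combination against counselling, which are the arms with the greatest and the least burden.

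**Working it through.** **1. Which reading of elimination fits the text?**

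- Non-adherence appears in both the elimination list and the stopping list. If the first list also did no more than end treatment, the repetition would serve no purpose.
- Incomplete data that affect the efficacy evaluation describe whether a patient can be evaluated. They make little sense as a reason to stop treatment.
- The explicit statement that data are kept for ITT is attached to patients stopped for drug intervention. The elimination list has no such clause. Read literally, a patient prescribed a drug is kept while one who self-medicates is eliminated.

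Removal from evaluation is therefore the more natural reading, though not the only possible one.

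**2. The plan's own figure.** Inputs from the Sample Size section: HAMD-17 means 5.70, 5.26 and 3.40; SDs 3.13, 3.11 and 2.97; power 0.90; α 0.05; dropout 10%; 46 per group.

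- Pooled SD = √[(3.13² + 3.11² + 2.97²)/3] = 3.07.
- Grand mean 4.787; sum of squared deviations = 0.834 + 0.224 + 1.923 = 2.981.
- Noncentrality = n × 2.981/3.07² ≈ 0.316n. One-way ANOVA power from the noncentral F is 0.8997 at n = 41 and 0.907 at n = 42.
- 41/0.9 = 45.6, rounded up to 46; 42/0.9 = 46.7, rounded up to 47.

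The stated 46 reproduces to within rounding. The 10% allowance leaves about 41 evaluable patients per group.

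**3. What exclusion could do to a two-arm comparison.** The documents give no elimination rates by arm and no outcomes of eliminated patients, so everything in this step is assumed. Let e be the share eliminated and D the excess HAMD-17 score of eliminated over retained patients.

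- Whole-arm mean μ = (1 − e)R + e(R + D), so the retained mean is R = μ − eD.
- With no true difference, bias = (e₂ − e₁) × D, in favour of the arm with more elimination when D is positive.
- SE = 3.07 × √(1/n₁ + 1/n₂). From 46 randomised, 10% eliminated leaves 41, 20% leaves 36 and 30% leaves 32. SE is 0.70 for 41 v 36 and 0.72 for 41 v 32.
- Two-sided type I error = 1 − Φ(1.96 − bias/SE) + Φ(−1.96 − bias/SE).

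| Eliminated | D | Bias (points) | Type I error |
|---|---|---|---|
| 10% v 20% | 1 | 0.1 | 5.2% |
| 10% v 20% | 2 | 0.2 | 5.9% |
| 10% v 20% | 3 | 0.3 | 7.1% |
| 10% v 30% | 1 | 0.2 | 5.9% |
| 10% v 30% | 2 | 0.4 | 8.6% |
| 10% v 30% | 3 | 0.6 | 13.2% |

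With equal e and equal D in both arms the bias is zero. Against the planned combination–counselling difference of 5.70 − 3.40 = 2.30 points, the range is 0.1/2.30 = 4% to 0.6/2.30 = 26%.

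**4. Loss of power.** With the same share eliminated in every arm, ANOVA power is 93.2% with none (46 per group), 90.0% at 10% (41), 85.5% at 20% (36) and 80.7% at 30% (32).

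**5. What counts as the prescribed treatment.** The EA Group section states "Participants will receive 24 sessions of acupuncture treatment (three times a week for 6 weeks; 30 min a session"), but 3 × 6 = 18. A patient who attends every session of the weekly schedule has 18/24 = 75% of the stated total. The Combination Therapy Group section repeats the mismatch. Failure to follow treatment is thus ambiguous in the two EA-containing arms and not in counselling. The total over 6 weeks is 6 sessions for counselling, 18 or 24 for EA, and 24 or 30 for combination.

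**The case against.** The strongest reply is that the elimination list never says anyone leaves the analysis. Its heading joins elimination with withdrawal, and withdrawn patients are to be described and imputed. The explicit rule for patients stopped for drug intervention keeps them for ITT. On that reading the passages are compatible. This stands in part: exclusion is not proven. It does not dispose of the point, because the incomplete-data item still fits poorly beside imputation, and two analysts could build different primary sets from the same text.

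A second reply is that analysis sets are commonly defined in an SAP or full protocol, which are not shown. That would answer a complaint about missing detail. Here the article itself states rules that pull against each other.

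A reader might also infer that exclusion would favour EA and combination, because patients doing badly would leave the more demanding arms. The documents do not support a direction. Self-medication could be commoner under counselling, which has the worst planned mean (5.7), and removing those patients would favour counselling. Some patients may stop because they feel better. Burden alone creates no bias; elimination must also be related to outcome and differ between arms.

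Finally, Table 2 item 5 might be taken as a rule for removing patients after randomisation. The Participants section applies Table 2 at entry, so its natural sense is concurrent treatment that would run into the trial. Its wording is loose beside the drug-intervention paragraph, but it is not a removal rule.

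**Conclusion.** The concern holds as a conflict in the text that must be resolved before analysis. The elimination criteria are most naturally read as removing randomised patients from evaluation for non-adherence, self-treatment or incomplete data. That cannot stand beside the stated ITT analysis and multiple imputation, and it fits poorly with keeping patients stopped for drug intervention in the ITT analysis.

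The consequence is conditional: if the list is applied as exclusions, the primary comparison may be biased. The illustrative size is 0.1 to 0.6 HAMD-17 points, with type I error of 5.2% to 13.2%. This assumes elimination rates of 10% v 20% or 10% v 30%, eliminated patients 1 to 3 points worse, SD 3.07 and no true difference. It is zero if elimination is equal and equally outcome-related. The documents do not establish that patients will be dropped, which arm would gain, or by how much.

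**What to change.** 1. State that all randomised patients are analysed in their allocated arm in the primary efficacy analysis.
2. Delete incomplete data as a ground for elimination and leave it to the multiple imputation already stated.
3. Confine the remaining items under Elimination and Withdrawal Criteria to discontinuation of study treatment or, at most, to a supportive per-protocol analysis.
4. Keep Table 2 item 5 as an entry criterion, and reconcile its reference to treatment during the trial with the drug-intervention paragraph under Combination Therapy Group.
5. Reconcile the stated number of EA sessions with the weekly schedule in both EA-containing arms, so that adherence has one meaning.

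Items 1 to 4 cost only wording in the protocol or SAP and leave the planned sample size unchanged. Item 5 is for the investigators to settle; this review takes no view on which figure is right.

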### Observation Criteria That Would Stop the Trial

Fail to adhere to the treatment requirement;Cases with serious adverse events that are not suitable for continued treatment;Serious clinical complications that occur in other clinical trials;The progression of disease during treatment.

### Sample Size

Sample size estimation uses a completely random design to compare multiple sample means. Target sample size was estimated using the PASS11 version, 1-β = 0.9, α = 0.05. According to a previous study (27), the mean of HAMD-17 in the psychological counseling group was 5.7, and the standard deviation was 3.13; the mean of HAMD-17 in the EA group was 5.26, and the standard deviation was 3.11; the mean of HAMD-17 in the combined therapy group was 3.4. The standard deviation was 2.97. To reduce the error, the target sample size was slightly enlarged, and a 10% dropout rate was estimated. Therefore, a sample of 46 participants will be the goal for each group in the proposed trial. A total of 138 patients will be aimed for in total.

### Intervention

According to the diagnostic criteria, inclusion criteria, and exclusion criteria, a total of 138 patients with sub-threshold depression will be randomly divided into three groups: EA group, counseling group, and combined therapy group.

### EA Group

Participants will receive 24 sessions of acupuncture treatment (three times a week for 6 weeks; 30 min a session; **Figure 2A**). According to traditional Chinese medicine theory, animal experiments (28, 29), and based on mutual consensus from clinical expert meetings, we will use acupoints GV20, GV29, and bilateral acupoints GB13 (**Figure 2B**) in the treatment. Disposable stainless steel needle insertion will be followed by performed stimulation, such as lifting and thrusting the needle combined with twirling and rotating the needle sheath (as shown in **Figures 2C**, **D**, the operation parameters of depth and frequency will be analyzed by acupuncture manipulation parameter tester [ATP-II; Shanghai Shangyou Medical Equipment Co. Ltd, Shanghai, China]), to produce the sensation known as deqi (sensation of numbness, soreness, radiating, or distention, which is considered to indicate effective needling) (30). One EA wire will be connected to the needle on acupoints GV20 and GV29, and another wire will be connected to the bilateral acupoints GB13. A continuous wave will be provided with a stimulation frequency of 2 Hz (31–33) and an intensity varied from 3 to 5 mA (34) until patients feel comfortable. Acupuncture will be performed by licensed acupuncturists with more than 3 years of clinical experience.

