**Methods:**

This study is a multicenter, randomized, single blind clinical trial that will be conducted in settings at four clinical centers in China. The randomized controlled trial (RCT) will examine the effectiveness of EA intervention, compared with counseling and combination therapy. A total of 138 sub-threshold depression patients (18 to 55 years of age with Beck Depression Inventory (BDI-II) score ≥ 14 points and Hamilton Depression Scale (HAMD-17) score: 7 points ≤ HAMD total score <17 points) will be recruited. The participants will be randomly assigned to receive the above treatments. The interventions will be delivered over a 6-week period (EA: 3 times a week for 6 weeks; 30 min a session. Counseling: once a week for 6 weeks; 50–60 min a session). The primary outcome measure will be the HAMD-17; BDI-II. The secondary outcome measures will be: Self-rating Depression Scale (SDS), Self-rating Anxiety Scale (SAS), and Pittsburgh Sleep Quality Index (PSQI). The assessments will occur at baseline, 2, 4, and 6 weeks and a follow-up period. Recruitment will commence in March 2020 and is anticipated to occur over a 2-year period.

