**Figure 2 f2:**
[figure not shown]
Procedure of EA and operation parameters. **(A)** Schematic protocol of EA manipulation (3 times a week for 6 weeks; 30 min a session). **(B)** Locations of acupoints. **(C)** Operation parameters for lifting and thrusting. **(D)** Operation frequency of twirling and rotation.

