###  Outcome Measures

The primary outcome measure is the HAMD-17 and BDI-II. Evaluation timelines are set as: before treatment, and the second, fourth, and sixth weeks of the treatment. HAMD-17 and BDI-II are widely used in the diagnosis and outcome evaluation of depression. The range of the HAMD-17 score is 0 to 52, with 25 scores or more indicating severe major depressive disorder, 18–24 scores indicating moderate, 7–17 scores indicating patients may have mild depression, and 0–6 scores indicating normal (36). The range of the BDI-II score is 0 to 63, with 29–63 scores indicating severe major depressive disorder, 20–28 scores indicating moderate, 14–19 scores indicating mild, and 0–13 scores indicating normal. The secondary outcome measures are SDS, SAS, and PSQI. The range of the SDS standard score is 0 to 100, with 72 scores or more indicating severe major depressive disorder, 63–72 scores indicating moderate, 53–62 scores indicating mild, and 0–53 scores indicating normal. The range of the SAS standard score is 0 to 100, with 70 scores or more indicating severe anxiety, 61–70 scores indicating moderate, 50–60 scores indicating mild, and 0–50 scores indicating normal. The range of the PSQI score is 0 to 15, where a lower score indicates better sleep quality. A score of 11–15 indicates poor quality of sleep, and a score of 0–5 indicates good quality of sleep (37). Evaluation time points are as follows: before treatment, and the second, fourth, and sixth weeks of the treatment, and a follow-up period. Participants will be followed up at 3, 6, and 12 months after treatment and will complete the SDS, SAS, and PSQI. In addition, functional MRI (fMRI) is an optional test under the attending physicians' supervision and instruction or depending on the patient's self-willingness. The fMRI, if included, will be performed in the resting state before the treatment and at the sixth week of treatment (38). The detailed procedures and parameters of fMRI are provided in **Supplementary File 1**. Also, the patient's blood samples and feces will be obtained twice before and after the treatment and will be used to build a biological sample bank, which could help with the research protocol moving forward.

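### The protocol states 24 electroacupuncture sessions in both arms that receive it, but its own weekly schedule gives 18, so the exposure under test is not uniquely defined

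*Protocol article*

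**What the plan says.** The EA Group section gives a total and a schedule in one sentence: "Participants will receive 24 sessions of acupuncture treatment (three times a week for 6 weeks; 30 min a session". The Combination Therapy Group section does the same for the arm that adds counseling: "Participants will receive 24 sessions of EA treatment (three times a week for 6 weeks; 30 min a session".

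Two other places give the schedule without a total. The Methods part of the abstract has "EA: 3 times a week for 6 weeks; 30 min a session", and the Figure 2 legend has "Schematic protocol of EA manipulation (3 times a week for 6 weeks; 30 min a session".

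The length of treatment is also stated separately in the abstract: "The interventions will be delivered over a 6-week period". Under Outcome Measures, HAMD-17 and BDI-II are assessed "before treatment, and the second, fourth, and sixth weeks of the treatment", so week 6 is the last listed time for those two scales.

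Two sections refer to adherence without a number. Elimination and Withdrawal Criteria lists "Those who fail to follow the prescribed treatment" and "Subjects with poor compliance". Observation Criteria That Would Stop the Trial lists, in different words, failure to keep to what the treatment requires. Neither gives a session count, a percentage or a threshold.

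**The concern.** The number of EA sessions is part of the definition of the treatment being tested. Here the total and the schedule disagree inside a single sentence, and they do so in both arms that receive EA. Three things could follow.

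- **Exposure.** Four hospitals will deliver EA. If one worked to the total and another to the schedule, participants in the same arm would receive different amounts, and the trial report could not say simply what was tested.
- **Timing.** If the total were reached at three sessions a week, EA would still be under way at the week-6 assessment, whereas counseling ends at six weeks. The follow-ups at 3, 6 and 12 months are counted from the end of treatment, so they would move too.
- **Compliance.** The elimination and stopping criteria refer to the prescribed treatment. If that were read as 24 sessions, a participant who missed no scheduled visit could appear to fall short. This could happen only in the two EA arms, so any such misclassification would differ between arms.

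**Working it through.** **Inputs**

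- Stated total: 24 EA sessions (EA Group; Combination Therapy Group).
- Stated schedule: 3 a week for 6 weeks, 30 minutes each (the same two sections, the abstract and the Figure 2 legend).
- Planned size: 46 per group, 138 in all (Sample Size).

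**Step 1. Try to reproduce the stated total.** Sessions = sessions per week × weeks = 3 × 6 = 18. The stated 24 is not reproduced.

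**Step 2. Size of the gap.**

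- Sessions: 24 − 18 = 6.
- Minutes: 18 × 30 = 540 and 24 × 30 = 720.
- Relative to the schedule: 24/18 = 1.33, so 24 is 33% more than 18. Relative to the total: 18/24 = 0.75, so 18 is 25% less than 24.
- Participants in arms with EA: 2 × 46 = 92 of 138.

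**Step 3. What would make 24 true.**

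- Six weeks kept: 24/6 = 4 a week, against the frequency given in all four places.
- Three a week kept: 24/3 = 8 weeks, against the duration given in all four places and the separate statement of a six-week period.

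**Step 4. Cumulative EA sessions at each assessment, under each reading.**

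| Reading | Week 2 | Week 4 | Week 6 | End of EA |
|---|---|---|---|---|
| 3 a week, 6 weeks | 6 | 12 | 18 | week 6 |
| 4 a week, 6 weeks | 8 | 16 | 24 | week 6 |
| 3 a week, 8 weeks | 6 | 12 | 18 | week 8 |

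The four-a-week reading changes how much EA has been given at every on-treatment assessment. The eight-week reading leaves those amounts as they are, but places the week-6 assessment two weeks before EA ends.

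**Step 5. Effect on compliance, if it were judged against the total.** Full attendance on the stated schedule is 18 of 24 sessions, or 75%. Judged against the schedule, the same attendance is 18 of 18, or 100%.

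**Step 6. Look for a reconciling statement.** The article mentions no loading, make-up or additional EA sessions, no fourth weekly session and no eight-week course. In the combination arm, 18 EA sessions plus 6 weekly counseling sessions happen to total 24. That does not explain the figure: the text there says 24 sessions of EA, and the EA-only arm has no counseling to add.

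**The case against.** The strongest reply is that the schedule is much less ambiguous than the total. Frequency and duration appear identically in four places, the six-week period is stated again on its own, and no other course is described anywhere. On this view 24 is a slip that most readers would see through. The effect on the analysis is also limited: the plan specifies an intention-to-treat analysis with multiple imputation, and neither the sample size nor any outcome definition or test uses the session count.

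The statements about the analysis stand. The count of appearances shows which figure is repeated more often, but it does not tell a site which one is intended. The total is itself stated twice, in the two sections that define the interventions. The article being a condensed version does not help either, because both figures are printed in full side by side.

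Three stronger readings are tempting, and the document does not support them.

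- A reader might infer that the protocol uses a wrong adherence denominator and so will label fully adherent participants as non-compliant. It defines no denominator or threshold, so the 75% is conditional.
- A reader might infer that sites could give different amounts and all be following the text. No site can follow all of it: one giving 18 departs from the total, and one giving 24 departs from the stated frequency or duration.
- A reader might infer that the primary assessment at week 6 would fall before treatment ends. Outcome Measures lists weeks 2, 4 and 6 without naming any of them as primary, and treatment beyond week 6 would itself contradict the six-week period.

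**Conclusion.** The contradiction is established by the document's own figures and needs no outside assumption: 24 sessions and three a week for six weeks cannot both be right. The discrepancy is 6 sessions (180 minutes) per participant, in two of three arms. It lies in the definition of the tested intervention, which is why it should be corrected even though no power figure or test depends on it.

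The consequences are conditional. EA running to week 8 assumes that a site works to the total at three a week. The 75% assumes that compliance is judged against 24. Different exposure across hospitals assumes that they resolve the conflict differently. Each is a risk that the present wording leaves open, and the document does not show that any of them will happen. Nor does it settle which figure is intended.

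**What to change.** Reconcile the EA Group section, the Combination Therapy Group section, the abstract and the Figure 2 legend, so that total sessions, weekly frequency, duration and the timing of the week-6 assessment agree. State that compliance, under both Elimination and Withdrawal Criteria and Observation Criteria That Would Stop the Trial, is judged against that single count. The investigators must say which figure is intended; this review takes no position on it.

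The cost is about one line in the protocol. Case report forms and site training material are not shown. If they carry the same total, they need the same correction. The change should be made before EA is delivered, because differences in exposure between sites cannot be undone afterwards.
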